### Inclusion and exclusion criteria

Eligible primary care practices must meet the following inclusion criteria:

Caring for adult patients ≥18 years old.Able to request natriuretic peptide blood testing (a standard screening test for HF in patients with symptoms) and initiating the HF diagnostic pathway recommended by the NICE^35^.

Exclusion criteria:

Poor WiFi and/or mobile data connectivity within primary care consulting rooms, prohibiting the use of the AI-enabled stethoscope.Not providing face-to-face patient consultations.

### Patient and public involvement

Patients were involved in the conception and trial design via a patient steering group and through online survey of over 10 000 patients at Imperial College Healthcare NHS Trust, UK. The study design was further developed in collaboration with the Pumping Marvellous Foundation, the UK’s largest patient-led heart failure charity and their Patient Educator group.

### Enrolment

Potential participating primary care practices will be approached by their parent NHS organisations: the North West London (NWL) Integrated Care System or Betsi Cadwaladr University Health Board (BCUHB), in England and Wales, respectively. Additionally, in NWL, primary care practices will be approached by the National Institute for Health and Care Research Clinical Research Network, whose mandate is to widen access to and diversify research participation. Practices expressing an interest will be contacted by the study team with up to two further follow-up emails and a subsequent phone call if necessary. Written informed consent will be recorded from leadership at each participating practice. Clinicians at all practices will be asked to complete a baseline questionnaire measuring their confidence in detecting and managing cardiovascular disease. The study team will have no direct contact with patients.

### Randomisation

Practices will be randomised 1:1 to the intervention or control arms using a validated, automated and audited randomisation tool (Sealed Envelope, London, UK)^40^ with allocation concealment. Practices will be notified of their treatment allocation by email.

### Intervention arm: AI-enabled stethoscope

This study will investigate the impact of an AI-enabled stethoscope (henceforth referred to as AI stethoscope) with integrated sensor technology—electrodes and a microphone—for recording digital single-lead ECG and PCG (Eko DUO, Eko Health Inc, California, USA). The AI stethoscope works as a conventional stethoscope with diaphragm and detachable tubing that enables conventional auscultation, with other features including noise filtration and cancellation. The device connects to an app on the user’s smartphone (Eko: Digital Stethoscope+ECG, Eko Health, USA) using Bluetooth connectivity for waveform visualisation. Connectivity via cellular/Wi-Fi allows access to cloud-based AI algorithms for analysis of waveforms (no data is stored in the AI stethoscope or user’s smartphone).

The AI stethoscope and associated AI algorithms are regulated by the UK Medicines and Healthcare Products Regulatory Agency (MHRA) and are UKCA-marked as Class IIa medical devices, respectively. This means that they are authorised for use in clinical care in the UK, in accordance with their regulated intended purpose.

The AI stethoscope is provided as a replacement stethoscope for routine patient clinical examination. Use of the AI stethoscope will be at the discretion of the responsible clinician, with no patient-level inclusion or exclusion criteria. The additional functionality in the form of AI algorithms for HFrEF, AF and VHD detection will be used within its regulated intended purpose. As established by previous studies,^26^ the optimum unit of examination to derive AI insights entails placing the device–‘listening’–over the pulmonary position (upper left sternal border) and taking a 15-s recording.

In an NHS first, the clinical guidelines for actioning AI outputs have been agreed by the Cardiovascular Executive Groups of the NHS North West London Integrated Care System and Betsi Cadwaladr University Health Board (online supplemental figure 1). Patients will be examined with the AI stethoscope in accordance with these guidelines, and/or where stethoscope examination is deemed clinically appropriate by the primary care clinician. Patients will provide verbal consent for examination with the AI stethoscope as per any physical examination performed by healthcare professionals for direct care purposes, in accordance with UK law and General Medical Council guidelines.^41^

Primary care clinicians at practices in the intervention arm will be provided with one session of in-person training in the use of the AI stethoscope. The training includes:

Delivery and setup of the AI stethoscope in each consultation roomSmartphone application installation and login (for either iOS or Android systems) on each clinician’s smartphone for the use of the AI stethoscopePairing of all clinician smartphones with all AI stethoscopes in the same practiceDemonstration of patient examination, single-lead ECG capture from the ‘spot check’ auscultation position and AI recommendationTroubleshooting signal captureVisual summary sheet for patient examination and troubleshooting affixed next to AI stethoscope in each consultation roomUpdate on the local clinical guideline and summary sheet affixed next to the AI stethoscope in each consultation room (online supplemental figure 1)

If any clinicians (who can initiate diagnostic pathways for HF, AF or VHD) decline to install the application on their smartphone, this will be logged by the study team.

GP practices in the intervention arm will receive six monthly updates (three total) from the clinical research team. These will be communicated via direct email to a nominated clinician from each practice team and include relevant data on numbers of positive screening results and subsequent clinician actions such as specialist referrals and implemented medical therapies. The reports will include monthly results of the following:

Number of patients with positive screening resultsProportion of patients with positive screening results referred for specialist reviewProportion of patients with positive screening results receiving guideline-direct medical therapies

At the end of the study, clinicians in the intervention arm will be asked to complete a validated usability questionnaire for the AI stethoscope (System Usability Scale).^42^

### Control arm

Primary care practices in the control arm will continue with usual clinical care, with decision-making for consideration of HF, and initiation of the NICE diagnostic pathway based on clinical judgement alone.

Participating practices can withdraw at any time. If a primary care practice ceases face-to-face consultations during the study, they will be withdrawn from the study by the research team.

### Data sources

In the NWL ICS, patient-level complete primary and secondary care clinical and cost data is pseudonymised and pooled within Discover-NOW, a UK Trusted Research Environment.^37^ AI stethoscope usage statistics and AI predictions will be integrated into the Discover-NOW and tagged to appropriate patient records. The study team will access this real-world data platform to measure population-level clinical and health economic outcomes, in addition to patient-level sensitivity analyses for NWL ICS.

At BCUH, only the direct care team will access medical records and record population-level outcomes as part of a service evaluation (coprimary endpoints), using epidemiological methods only.

### Study outcomes

Outcomes are summarised in box 1.

Box 1Study outcomesStudy outcomes comparing intervention and control groupsCoprimary endpointsIncidence of coded new diagnoses of HFRatio of coded diagnoses of HF via hospital admission-based versus community-based pathwaysSecondary endpointsNew coded diagnoses of atrial fibrillation (AF)New coded diagnoses of valvular heart disease (VHD)Cost-consequence differential (HF, AF, VHD)Health service utilisation for diagnosticsPrescription of guideline-directed medical therapy for HF, AF, VHDNew implantation of cardiac resynchronisation therapy (CRT) and/or implantable cardiac defibrillator (ICD) devicesDifferential rates of uptake and utilisation of AI stethoscope in primary careDeterminants of utilisation of AI stethoscope in primary careQuality of life–healthy days at home (HDAH)^50 51^Independent variables for sensitivity and subgroup analysesGP practice population social deprivationGP practice national target performanceGP practice clinical staffing model

### Statistical analysis

Baseline patient-level data in NWL will be extracted at the index date, defined as the date of first examination using the AI stethoscope at each primary care practice. Data will be summarised as mean (SD) or median (IQR) for skewed data. Comparisons between groups will be undertaken on an intention-to-treat basis, using two-sample t tests for continuous variables, and χ^2^ tests for binary and categorical variables. For each outcome, we will perform generalised mixed-effect logistic regression to compare the study arms, with the GP practice as a random effect.

Subgroup analyses for patient-level outcomes will be performed, stratified by age, sex, ethnicity and geography, patient comorbidities and GP practice characteristics (mean age of clinicians, size of clinical team, number of registered patients).

Patient-level sensitivity analyses will be performed for patients with abnormal AI-stethoscope predictions for HF to identify direct associations between AI stethoscope predictions and specific diagnostic codes for HF, AF and VHD.

We will measure relationships between items in the clinician questionnaire, utilisation rates of the AI stethoscope, compliance with recommendations and the primary endpoints. These analyses will identify domains that are most strongly related to utilisation and compliance, which will help improve the technology, and guide future implementation and clinical pathways.

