### Study design

TRICORDER is an open-label, two-arm cluster-randomised controlled trial. Taking a decentralised approach, primary care practices in the NHS North West London Integrated Care System (NWL ICS, 2.8 million residents, figure 2) and the Betsi Cadwaladr University Health Board (BCUHB, 670 000 residents) in North Wales, UK, will be enrolled for 18 months.

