### Interim analysis

An interim analysis will be performed 6 months after the first site has been randomised. The interim analysis will report the following selected outcomes and will be reviewed by the Trial Steering Committee, who will remain blinded to the treatment allocation of each group until the study end:

Coprimary endpoints:

Difference in the incidence of coded HF between groups;Difference in the ratio of coded HF incidence via hospital admission-based versus community-based diagnostic pathways between groups

Secondary endpoints

Healthcare diagnostics utilisationPrimary care appointmentsEmergency department presentationsNon-elective hospital admissionsAI stethoscope utilisation ratesCompletion of site setup for all practices in intervention groupData fidelity—ascertainment

The following interim outcomes will be considered significant and warranting intervention:

Mean AI-stethoscope utilisation rate of less than five recordings per month per practice in the intervention armHealthcare diagnostics utilisation differential affecting patient safetyIncomplete site setup in intervention group

In keeping with formative evaluations in implementation research^29^,^31^ and behavioural change frameworks,^43^ adaptive interventions will be considered prospectively to maximise the success of the implementation of AI stethoscope (given the established confidence for the technology ‘working’ on the basis of widely validated statistical accuracy). In addition, prespecified interventions will be available to the Steering Committee following the interim analysis.

Semistructured interviews of high- and low-use participantsProvision of repeat training in the use of the AI stethoscopeRedistribution of the AI stethoscope to new, prospectively enrolled GP practicesProvision of latest generation of the AI stethoscope hardware and software to intervention groupIntegration of the AI stethoscope system with the electronic health record system

To mitigate lead-time effects, interim analysis of the coprimary endpoints will not incur a stopping rule at 6 months. If at 6 months there is no statistically significant difference between treatment arms for the coprimary endpoints, then a further interim review will be performed at 12 months. If there remains no clinically significant difference in the coprimary endpoint at 12 months, the Trial Steering Group will have the option to stop the trial on the basis of futility.

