This study is both decentralised and principally uses ‘real-world’ data; there is no lead/central study site or logistics/travel outside each GP practice. Each will contribute data equally, but without the need to complete any study-specific (cumbersome) data collection instruments. Instead, our use of Discover-NOW enables outcomes measurement with routinely recorded (real world) data. The platform’s offer of comprehensive linked (primary and secondary care) clinical and cost data affords patient-level sensitivity analyses. This will allow robust measurement of associations between diagnostic outcomes and use of the AI stethoscope. Separate to such novel elements of this study, TRICORDER has set several other important precedents for translational AI research, including approval of the first regional NHS clinical guideline for the use of a primary care focused AI technology, and sector-wide data governance approval covering use of an AI technology across hundreds of disparate primary care sites.

This research protocol is best interpreted in the context of its limitations. The pragmatic design, which aims to have a minimal impact on GP workflows, may in some cases limit sustained use of the technology by not setting any expectations or requirement for use—though this may somewhat mitigate any Hawthorne effect.^49^ This study is the first to accompany a novel AI technology with an NHS sector-approved clinical guideline for use, but variable adherence may limit the impact attributable to the technology. This will be addressed systematically, taking an implementation science approach to maximise uptake of the intervention. Finally, the examination of real-world data is universally limited by the inconsistency and variable fidelity of medical coding in capturing specific variables of interest. For example, for HF, this is rarely coded with a granularity that describes preserved, moderately reduced or reduced ejection fraction. However, the otherwise comprehensive data flows associated with this study will allow holistic scrutiny of a broad selection of outcomes that need to be understood to underpin any recommendations for system-wide uptake. Ultimately, this will serve to provide a realistic estimate of the potential clinical and health economic impact of the AI stethoscope technology in NHS primary care.

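### The baseline index date is the first AI-stethoscope examination at a practice, so it does not exist in the control arm and depends on uptake in the intervention arm

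*Protocol article*

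**What the plan says.** The Statistical analysis section gives one definition: "Baseline patient-level data in NWL will be extracted at the index date, defined as the date of first examination using the AI stethoscope", with the date set separately for each practice. The same paragraph adds: "Comparisons between groups will be undertaken on an intention-to-treat basis". It names two-sample t tests and chi-squared tests for the group comparisons and a mixed-effect logistic model for each outcome. The next paragraph plans patient-level subgroups by age, sex, ethnicity, comorbidity and other factors.

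On who can have such a date:

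- Control arm: "Primary care practices in the control arm will continue with usual clinical care".
- Intervention arm: "Use of the AI stethoscope will be at the discretion of the responsible clinician, with no patient-level inclusion or exclusion criteria".
- Discussion: the design "may in some cases limit sustained use of the technology by not setting any expectations or requirement for use".
- Interim analysis: incomplete set-up and low mean use in intervention practices are listed as findings that call for action.

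On other dates, the Randomisation section says "Practices will be randomised 1:1 to the intervention or control arms", with allocation notified by email. The Study design section says that practices "will be enrolled for 18 months", without naming the day on which the 18 months begin. The Interim analysis section uses a trial-level clock: "An interim analysis will be performed 6 months after the first site has been randomised".

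**The concern.** A baseline date in a randomised comparison has to exist for every randomised unit and must not depend on what happens after allocation. This one fails both requirements. It is defined by an event that only one arm can experience, and within that arm its timing reflects delivery, training, app installation and clinicians' interest.

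What is directly at stake is the baseline description of the arms and every covariate or subgroup measured at baseline. If age, comorbidity or existing diagnoses are read from the record at first use in one arm and at some improvised date in the other, the two sets of values are not like for like. Outcomes come from routine records that can be cut at any date, so an analyst who has to choose a control date later could choose it with the data in view.

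A further risk follows if the same date is reused to separate prevalent from new heart failure, or to start the outcome window. The first coprimary endpoint is new coded heart failure, so some start date is needed, and the index date is the only practice-level baseline date that the article defines.

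**Working it through.** The article attaches no figure to this definition, so there is nothing to reproduce. The check is whether the rule can be applied to each group of practices.

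**Step 1. Apply the rule**

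| Group | Does the index date exist? | Relation to randomisation |
|---|---|---|
| NWL control practices | No: usual care, no device | not applicable |
| NWL intervention practices with no use | No | not applicable |
| NWL intervention practices with at least one use | Yes | after randomisation, dependent on uptake |
| North Wales practices | Rule not applied: only population-level coprimary outcomes are recorded there | not applicable |

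The article gives no substitute date for the first two rows.

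**Step 2. Count the practices affected**

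Inputs from Sample size and Randomisation: 200 practices anticipated, allocated 1:1; eligible sites 350 in NWL out of at least 400.

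- Control practices in the whole trial: 200 / 2 = 100.
- NWL share, assuming recruitment follows the eligible sites: 350 / 400 = 0.875.
- NWL control practices without an index date: 100 × 0.875 = 87.5, about 88.

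The abstract gives 200 as a ceiling, so the number could be smaller. The proportion of NWL control practices affected is 100% whatever the total. The number of never-using intervention practices cannot be derived from the article.

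**Step 3. Conditional illustration only**

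The article does not start outcome follow-up at the index date. Suppose that it did, that controls were started at randomisation, that both arms ended at 18 months from randomisation, and that the model had no person-time term. Let L be the months from randomisation to first use (assumed; the article gives no value). For rare events:

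- ratio of counts with no true effect = (18 − L) / 18;
- apparent ratio under the planning rates = (0.79 / 0.62) × (18 − L) / 18, where 0.79 / 0.62 = 1.27.

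| L (months) | Intervention follow-up (months) | Ratio, no effect | Apparent ratio, planned effect |
|---|---|---|---|
| 1 | 17 | 0.94 | 1.20 |
| 3 | 15 | 0.83 | 1.06 |
| 6 | 12 | 0.67 | 0.85 |

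This shows only how sensitive the comparison would be if the date were carried over to follow-up. It does not estimate bias in the plan as written.

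**The case against.** The strongest reply concerns scope. The sentence covers baseline extraction, at patient level, in one region. The coprimary endpoints are population-level incidence and pathway ratio, and the 18-month enrolment is not tied to first use. A reader might infer three stronger things:

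- **Diagnoses between randomisation and first use are lost from the intervention arm only.** The article does not support this, because nothing in it starts outcome counting at the index date.
- **Practices that never use the device leave the analysis, against intention to treat.** Nothing restricts the analysis set to practices with an index date. Incomplete set-up is an interim trigger for corrective action and not a ground for exclusion, and the Discussion speaks of sustained use, which is not the same as never using the device. Zero-use practices are possible but not predicted.
- **Half of the trial's practices are affected.** That would count North Wales, where the rule does not apply.

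This part of the reply stands, and the point is limited accordingly.

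A second reply is that this is a condensed article, and the full protocol or analysis plan may assign control practices a corresponding date. That would be fair if the article had left the index date open. It did not: it states a definition that one arm cannot meet. A fuller document may already repair this, but the published wording still needs correcting.

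Third, randomisation is not the only workable anchor; a common calendar date or a matched date for controls would also serve. That is true, but the randomisation date already exists for every practice and needs no matching rule.

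**Conclusion.** Wrong as written; it should be fixed. The NWL baseline index date is undefined for all control practices and for any intervention practice that never uses the device. Elsewhere it is a post-randomisation date shaped by set-up and uptake. The baseline comparison and patient-level subgroups cannot be produced on a common footing from this rule. That conclusion rests on the text alone. The figure of about 88 control practices rests on 200 practices being recruited in proportion to the eligible sites.

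Bias in the coprimary comparison is a risk, not a documented fact. It arises only if follow-up or new-diagnosis status is also anchored to first use, and its size then depends on an assumed lag. This is why the point is not rated as something that invalidates the primary analysis.

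**What to change.** Define the index date in both arms as the date on which the practice was randomised (or notified of its allocation). Extract baseline data at that date for all randomised NWL practices, whether or not the device was used. State that the 18-month outcome window starts from the same date in both arms. Keep the date of first AI-stethoscope examination only as an uptake variable in the intervention arm.

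The cost is a change of wording, because a randomisation date exists for every practice. The statistical cost is that set-up time counts in intervention follow-up. If the planned ratio of 1.27 applied only once the device was in use, the 18-month ratio would be 1 + 0.27 × (18 − L) / 18: about 1.26 for an assumed lag of 1 month and about 1.23 for 3 months. That dilution is part of the effect of offering the device, which is what an intention-to-treat comparison is meant to estimate.

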**Figure 2 F2:**
[figure not shown]
Map of London, with the boroughs of North West London stratified by Index of Multiple Deprivation deciles

Each individual primary care practice employing GPs serves as a cluster—the unit of participation and randomisation. Each participating cluster will variously employ GPs, practice nurses, physician associates and other healthcare professionals who constitute the care team. This unit of recruitment was chosen because the NHS' clinical, financial and information governance processes are standardised at this level.

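### Unclustered t and chi-squared tests are prescribed between arms alongside a mixed logistic model, with no ranking, and for costs, utilisation counts and healthy days the unclustered test is the only stated analysis that fits

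*Protocol article*

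**What the plan says.** The Study design section of the protocol article makes the practice "the unit of participation and randomisation", and the Randomisation section adds: "Practices will be randomised 1:1 to the intervention or control arms". The Sample size section assumes an intracluster correlation of 0.01.

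The Statistical analysis section opens with baseline material ("Baseline patient-level data in NWL will be extracted at the index date") and a sentence on summary statistics. It then states: "Comparisons between groups will be undertaken on an intention-to-treat basis, using two-sample t tests for continuous variables", and names chi-squared "tests for binary and categorical variables". No adjustment for practice is mentioned, and the sentence is not confined to baseline variables.

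The following sentence reads: "For each outcome, we will perform generalised mixed-effect logistic regression to compare the study arms, with the GP practice as a random effect".

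Box 1 (Study outcomes) lists coded diagnoses, prescriptions and device implantation. It also lists a hospital-to-community ratio of heart failure (HF) diagnoses, a cost-consequence differential, health service utilisation for diagnostics, and healthy days at home.

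**The concern.** Three things follow from the two sentences read together.

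- A patient-level t or chi-squared test in a practice-randomised trial treats patients of one practice as independent. Its standard errors are too small and it rejects a true null too often.
- A binary outcome receives an unclustered and a clustered p-value, with no rule on which counts. This matters at the interim stage: under the Interim analysis section, whether a further review is held at 12 months depends on whether the coprimary endpoints differ significantly between arms at 6 months. The two tests can disagree on that.
- One logistic model is laid down for all outcomes, but costs, utilisation counts and days at home are not binary. Under the stated rules they are left with the t test. The Discussion says the trial is meant to support NHS-wide commissioning, so the cost result is not peripheral.

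**Working it through.** **Inputs.** From the Sample size section: 200 practices, 60 eligible patients per practice per year, intracluster correlation (ICC) 0.01, two-sided alpha 0.05, HF rate 0.62 per 1000 per year. From Study design: 18 months. From Setting: average list 8500. Allocation is 1:1, so there are 100 practices per arm, and 100 × 60 = 6000 per arm, which reproduces the plan's own figure.

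**Size of an unadjusted patient-level test.** The design effect is DE = 1 + (m − 1) × ICC. The true two-sided type I error at nominal 5% is 2 × [1 − Φ(1.96/√DE)]. With DE = 1 this returns 0.05, as it should.

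| Patients per practice (m) | ICC | DE | True type I error |
|---|---|---|---|
| 60 (plan) | 0.01 (plan) | 1 + 59 × 0.01 = 1.59 | 2 × [1 − Φ(1.96/1.261)] = 0.120 |
| 90 (60 per year × 1.5 years) | 0.01 (plan) | 1 + 89 × 0.01 = 1.89 | 2 × [1 − Φ(1.96/1.375)] = 0.154 |
| 60 (plan) | 0.001 (assumed) | 1.059 | 0.057 |

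At DE 1.59 a correct confidence interval is √1.59 = 1.26 times as wide as the unadjusted one.

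**Simulation check.** With 100 practices per arm, 60 patients each, ICC 0.01 and 4000 replicates, the patient-level t test rejected in 0.119 of null trials. The chi-squared test rejected in 0.110 (outcome proportion of 0.3 assumed). A t test on practice means rejected in 0.049, so the fault lies in the unit of analysis and not in the t test itself.

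**HF incidence on whole lists.** The 12% describes 60 patients per practice, not HF incidence on registered lists. For the latter, the expected count per control practice over 18 months is 8500 × 0.00062 × 1.5 = 7.9, and DE = 1 + 7.9 × k², where k is the between-practice coefficient of variation. The protocol does not give k. Assuming k = 0.3 gives DE 1.71 and error 0.134; k = 0.5 gives DE 2.98 and error 0.256.

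**Which stated analysis fits which outcome.**

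| Outcome (Box 1) | Type | Mixed logistic with practice effect | t or chi-squared as stated |
|---|---|---|---|
| New coded HF, atrial fibrillation (AF), valvular heart disease (VHD) | binary | fits | unclustered |
| Hospital versus community route | binary among coded HF cases | fits | unclustered |
| Guideline therapy, device implantation | binary | fits | unclustered |
| Costs | continuous | does not fit | unclustered; only stated option |
| Diagnostic utilisation | count | does not fit | unclustered; only stated option |
| Healthy days at home | days | does not fit | unclustered; only stated option |

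On the second row: if p is the proportion diagnosed through hospital, the hospital-to-community ratio is p/(1 − p). That is an odds, and a logistic model compares odds between arms.

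**The case against.** The best defence is that clustering is handled. The only sentence that speaks of outcomes is the one with the practice random effect. The t and chi-squared sentence follows baseline material and refers to variables, so it can be read as description. A single model for all outcomes may also be condensed article wording, because Box 1 includes determinants of stethoscope use, which cannot be an arm comparison. Models for costs and days often sit in an analysis plan or health-economic plan, which is not shown.

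Much of this stands. Both coprimary endpoints have a usable clustered analysis. But the intention-to-treat wording points to outcomes, the tests are not limited to baseline, and no ranking is given. The choice of model is not left open either: the article fixes logistic regression for all outcomes.

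Four stronger readings are tempting, and the document does not support them:

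- **That the trial ignores clustering altogether.** The random-effect sentence rules this out.
- **That the coprimary ratio cannot be analysed by logistic regression.** Route is binary among coded cases and the ratio is its odds.
- **That HF incidence, or the inclusion of North Wales, requires a person-time model.** The Data sources section says the North Wales team will "record population-level outcomes as part of a service evaluation (coprimary endpoints), using epidemiological methods only". Mixed logistic regression can be fitted to grouped counts per practice. At an 18-month risk of 0.62 × 1.5 = 0.93 per 1000, odds ratio and risk ratio nearly coincide.
- **That the error rate reaches 83%.** This results from applying ICC 0.01 to lists of 8500 (DE 85.99). At a risk of 0.00093, ICC = k² × p/(1 − p) = 0.01 requires k of about 3.3, which is not a plausible variation between practices.

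**Conclusion.** The point holds in limited form. The article prescribes unclustered between-arm tests without confining them to baseline, and does not say whether they or the mixed model govern inference. For binary outcomes, both coprimary endpoints included, a sound analysis is already stated and only its precedence is missing. For costs, diagnostic utilisation and healthy days at home, the only stated analysis that fits the data has the wrong error rate.

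The size is about 12% true type I error in place of 5%, on the plan's 60 patients per practice and ICC of 0.01. This assumes that the tests are run on patient-level data, that practices contribute equally, that the ICC applies to the outcome tested, and that the test is used for inference. The figure moves with those inputs: about 6% at an assumed ICC of 0.001, about 15% at 90 patients per practice, and 13% to 26% for list-based HF incidence under the assumed between-practice variation.

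**What to change.** 1. Remove the two-sample t and chi-squared tests between arms, or confine them to description without inference.
2. State that the mixed model with a practice random effect is the sole basis for between-arm inference, including at the 6- and 12-month interim reviews.
3. Replace the single logistic rule with one by outcome type: mixed logistic for binary outcomes and for route of diagnosis among coded HF cases; a count mixed model for diagnostic utilisation; a linear or gamma mixed model for costs and healthy days at home.
4. Optional: a Poisson or negative-binomial model with a person-years offset for HF, AF and VHD incidence. It handles joiners and leavers better, but it does not correct an invalid model.

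If an analysis plan already specifies this, the protocol wording should be brought into line with it. The cost is rewording and modest programming, with no new data. Confidence intervals become wider than the unadjusted tests would give, by about 26% at the plan's own figures (√1.59 = 1.26), and that width is the correct one.
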